#### Data Analysis

Descriptive analysis will be performed on baseline characteristics and covariates. We will use paired *t* test to determine the significance of the change in measured parameters during test diets. Multiple regression will be used to assess the determinants of insulin secretion after adjusting for covariates. Dietary order will be included in multiple regression models as a between participant variable. Carryover effects will be tested in an expanded model including diet and period interaction when evaluating the effects of diet over the 2 test periods. Period effects refer to a change between intervention and measurement periods and within subjects, which would have occurred independently from any diet given. Plausible period effects in diet-based trials might arise from behavioral changes by participants as a result of enrolment in a dietary-based trial

Adjustment to *P* values for multiple comparisons will be performed using the Holm method, and statistical significance will be assumed when *P*<.05.

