## Methods

### Study Design and Setting

#### Overview

This study has a randomized, two period double-blind cross-over design (Figure 1). We aim for 20 overweight but otherwise healthy normoglycemic adults, aged 18-50 years to complete the trial. Participants will commence the study after a 2-week run-in on their habitual diet, but with restricted intake of alcohol, fast food, and coffee. Test diets will then each be followed for 2 weeks, separated by a 4-week washout period (return to habitual diet). Usual levels of physical activity will be continued throughout the study. Overweight participants will be selected for enrolment in this study as they represent the average Australian population, are generally more insulin resistant, more sedentary, and have higher levels of inflammatory markers, all factors that increase their risk for type 2 diabetes [17,18]. Participants will be sought using a number of advertising strategies including posters, flyers, newspaper, and online advertising and email newsletters from the Alfred Hospital in Melbourne, Australia.

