### Statistical Considerations

#### Sample Size Calculation

The sample size is estimated on the basis of the primary hypothesis including being able to detect a 20% difference in insulin sensitivity following dietary AGE modification using G*Power, an online tool to compute statistical power analyses. This effect size is clinically significant and similar to that seen after a 6-month intervention period using troglitazone, an insulin sensitizing therapy. Troglitazone improved insulin sensitivity as measured by glucose clamp in obese, non-diabetic individuals [19] whose initial glucose disposal rate was 8.1 (+2.0) mg/kg/min. To detect a 20% difference in insulin sensitivity in a cross-over design by paired *t* test, we will require complete data from 20 individuals (power 80%, alpha 5%, SD 1.0).

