### Randomization and Blinding

Following successful screening and baseline assessment, subjects will be randomized by a computer program to commence the study with either the high or low AGE diet. Randomization will be done in blocks of four by gender using a relevant computer program to ensure balance in each test group and will be conducted by a researcher from within our department who is not involved in the trial data collection, analysis, or reporting. Diet type will be coded as (red or blue) by the dietitian, so that participants and blinded investigators remain unaware of which dietary period they are undertaking or how diet might affect glucose metabolism. Clinical and laboratory investigators will also be masked to diet allocation.

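### The planned diet-by-period test of carryover is the dietary-order contrast under another name, so a null result would be weak evidence that the washout worked

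*Protocol article*

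**What the plan says.** The Overview of the Methods states: "This study has a randomized, two period double-blind cross-over design". The two diets last 2 weeks each and are "separated by a 4-week washout period (return to habitual diet").

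Under Data Analysis, the change in each parameter is compared by paired t test. Multiple regression is then introduced for the determinants of insulin secretion, followed by: "Dietary order will be included in multiple regression models as a between participant variable". The next sentence is the one at issue: "Carryover effects will be tested in an expanded model including diet and period interaction". No power is given for this test, and no action is tied to its result.

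Under Sample Size Calculation, "we will require complete data from 20 individuals", with the settings "power 80%, alpha 5%, SD 1.0". Under Randomization and Blinding, "Randomization will be done in blocks of four by gender".

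The documents differ on how many measurements each period yields. The abstract's Methods paragraph expresses outcomes as change over each dietary period and has measurements at both the start and the end of each. Follow-Up Visits lists only visits after each diet.

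**The concern.** A carryover test is meant to show whether the effect of the first diet persists through the washout into the second period. In this design the chosen term cannot isolate that. It is a comparison between the two order groups, and those groups can differ by chance or because the diet effect truly differs between periods.

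Two misreadings are then possible. A non-significant result could be reported as evidence that 4 weeks of washout was enough. A significant result could arise from a chance group difference and prompt a switch to first-period data only, which would give up the within-person comparison and alter the error rate of the diet test.

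**Working it through.** **1. What the interaction estimates.** Code order *o*, period *p* and diet *d* as 0/1, with one value per participant per period. The four cells (*o*, *p*, *d*, *d×p*) are (0,0,0,0), (0,1,1,1), (1,0,1,0) and (1,1,0,0). In every cell

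*o = p + d − 2(d×p)*.

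Intercept, order, period and diet already have rank 4. Adding *d×p* gives 5 columns and the rank stays 4. Leaving order out and keeping *d×p* also gives rank 4, so it is the same model relabelled. With 20 participant effects plus period, diet and *d×p* there are 23 columns of rank 22. This step needs no assumed figure beyond one value per period.

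**2. The plan's own figure.** The only stated figure is N = 20 for the paired comparison. The target is 20% of 8.1, that is 0.20 × 8.1 = 1.62 mg/kg/min. If SD 1.0 is the SD of the within-person difference, a two-sided 5% paired t test needs 6 participants for 80% power, so N = 20 is not reproduced. N = 20 at 80% power corresponds to a standardised difference of 0.66, hence an SD of the difference of 1.62/0.66 ≈ 2.45. That mismatch is a separate matter. It is used here only to set the range of SDs, 1.0 to 2.45.

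**3. Power of the order contrast.** Inputs: 10 per order (20 completers, 1:1 allocation assumed from the blocks of four), two-sided 5%, 18 degrees of freedom, noncentral t on participant totals. The standard error is SD(total) × √(2/10).

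*End-of-diet values.* Assume a between-person SD of 2.0 (the spread printed beside 8.1 for the troglitazone cohort, read as an SD) and an SD of difference of 1.0. Then Var(total) = 4 × 2.0² − 1.0² = 15, SD(total) = 3.87 and SE = √(15 × 2/10) = 1.73.

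*Change scores.* Assume the two periods are uncorrelated, so SD(total) equals the SD of the difference. With 2.45, SE = 2.45 × √0.2 = 1.10; with 1.0, SE = 0.45. If SD 1.0 is instead the SD of each period's change, SD(total) = √2 = 1.41 and SE = 0.63.

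| Scale and SD assumed | Carryover 1.62 | 0.81 | 0.405 |
|---|---|---|---|
| End-of-diet, 2.0 and 1.0 | 14% | 7% | 6% |
| End-of-diet, 2.0 and 2.45 | 19% | 8% | 6% |
| Change, SD of difference 2.45 | 29% | 11% | 6% |
| Change, SD 1.0 per period | 68% | 23% | 9% |
| Change, SD of difference 1.0 | 93% | 40% | 14% |

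**4. What a change score hides.** If the first diet shifts the start and the end of period 2 by the same amount, the shift cancels from the change. The test then misses it whatever its power, although the diet contrast on change scores is not biased by it either. On end-of-diet values, a carryover contrast of 1.62 would bias the diet estimate by half of it, 0.81.

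**The case against.** Four points can be made for the plan.

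- **Order and the interaction are not clearly in one equation.** The order term follows the sentence on insulin secretion, and a fuller document may give the specification. This stands. A reader might infer that the plan fixes a rank-deficient model, but the text does not settle that. It does not rescue the test: without order, the interaction is the order contrast renamed.
- **Four values per person would change the algebra.** If start and end values of both periods enter one model, with diet active only at the end, the matrix with order, period, time, period-by-time, diet and diet-by-period has full rank (7 of 7). This also stands, so non-identifiability is conditional on one value per period. The interaction is still a comparison of change between the order groups, and Follow-Up Visits does not list the period-2 start measurements.
- **Near-zero power is too strong.** The 14% figure is on end-of-diet values, whereas the abstract analyses change. On change scores, power for a full-size carryover could reach 93%. This stands as a limit on the claim. That figure, however, needs both the smallest SD and a carryover as large as the whole target effect.
- **No harm is written into the plan.** A reader might infer a two-stage procedure in which this test chooses the analysis. The protocol contains no such rule and no first-period fallback. If the test is only reported, the error rate of the diet comparison is unchanged.

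**Conclusion.** The point holds in a limited form. With one value per period, the planned interaction is the dietary-order contrast. It therefore cannot separate carryover from a difference between order groups or from a true diet-by-period interaction. That part is exact.

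The strength of a null result depends on assumptions the document does not settle: the scale, the SD, 1:1 allocation and uncorrelated periods for change scores. Across the cases shown, power is 14% to 93% for a carryover of 1.62 mg/kg/min and 7% to 40% for half of that. A null result is weak evidence about the washout, most plainly for any carryover smaller than the full diet effect.

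This is a defect of the planned test, not a finding that the 4-week washout is inadequate or that the trial's data could never inform on it. Start-of-period values, if taken, would bear on the washout more directly. Distortion of the diet comparison is a risk that the silence on follow-up action leaves open.

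**What to change.** Under Data Analysis:

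1. Remove the diet-by-period interaction as a test of carryover.
2. State that the diet effect is always estimated from a model with diet, period and participant effects, whatever the order contrast shows.
3. Justify the 4-week washout on substantive grounds.
4. State whether the period-2 start measurements described in the abstract are taken, and bring Follow-Up Visits into line. If they are, report start-of-period values by order as a descriptive check that does not change the analysis.

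The cost is one uninformative test. The period-adjusted model also replaces the simple paired t test for the diet effect and uses one degree of freedom, leaving 18 instead of 19 with 20 completers. Items 1 to 3 need no added participants or visits.

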**Methods:**

Overweight, but otherwise healthy, non-diabetic adults (N=20) aged 18-50 years old will complete a randomized cross-over design intervention study alternating low and high (4-fold increase) AGE diets (2-week duration). At baseline, participants will undergo a medical review including an intravenous glucose tolerance test (IVGTT), a hyperinsulinemic-euglycemic clamp, and anthropometric measures and questionnaires assessing diet, physical activity, and general wellness. Each test diet will be followed for 14 days, followed by a 4-week washout period before commencement of the second alternate dietary period. Energy, macronutrient, and AGE intake will be calculated for each dietary period. Additionally, the AGE content of foods used in the study will be measured by ultra performance liquid chromatography mass spectrometry. All measurements will be repeated at the beginning and end of each dietary period. Primary and secondary outcomes will be expressed as a change over the dietary period for insulin sensitivity, secretion, anthropometric parameters, sRAGE, and inflammation markers and compared by paired *t* test and analysis of variance (ANOVA).

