### Outcome Measurements

The primary outcome in this trial is the difference (change) in insulin sensitivity between the 2 diets. Secondary outcomes include changes in insulin secretion, body weight, body mass index (BMI), waist, waist-to-hip ratio (WHR), resting systolic and diastolic blood pressure, lipid profile and markers of inflammation (ie, interleukin (IL)-1ß, IL-6, IL-8, and IL-10), tumour necrosis factor-α (TNFα), macrophage migration inhibitory factor (MIF), monocyte chemotactic protein-1 (MCP-1), C-reactive protein (CRP), nuclear factor-κB (NF-κB) activity, and circulating sRAGEs.

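### The primary paired t test has no period term although the plan calls period effects plausible; a period difference in the within-period change would inflate its standard error and, with unequal orders, bias it.

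*Protocol article*

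**What the plan says.** Outcome Measurements defines the target: "The primary outcome in this trial is the difference (change) in insulin sensitivity between the 2 diets". The Abstract (Methods) adds that outcomes are expressed as a change over each dietary period, with measurements at the beginning and end of each period.

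The test is named twice. Sample Size Calculation reads "To detect a 20% difference in insulin sensitivity in a cross-over design by paired" t test, with complete data from 20 people. Data Analysis reads "We will use paired *t* test to determine the significance of the change in measured parameters during test diets". Neither place gives a period or order term.

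Data Analysis then raises the period problem itself: "Period effects refer to a change between intervention and measurement periods and within subjects, which would have occurred independently from any diet given". The next sentence is "Plausible period effects in diet-based trials might arise from behavioral changes by participants as a result of enrolment in a dietary-based trial".

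Three other statements bear on period or order:
- "Multiple regression will be used to assess the determinants of insulin secretion after adjusting for covariates", followed directly by "Dietary order will be included in multiple regression models as a between participant variable".
- An expanded model with a diet and period interaction, whose stated purpose is to test carryover.
- The Abstract's mention of ANOVA alongside the paired t test, with no terms given.

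**The concern.** In a two-period cross-over, a period effect is added to the diet difference in one order and subtracted in the other. A paired t test that ignores order treats this systematic split as random scatter. If the two orders have unequal numbers of completers, part of the period effect also stays in the estimate. The plan names this nuisance effect and then specifies a primary test that cannot remove it.

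The design gives a concrete route to such an effect. According to the Overview under Study Design and Setting, period 1 follows a two-week run-in with alcohol, fast food and coffee restricted, while period 2 follows a four-week return to the usual diet. Participants may therefore start the two periods in different states, and the change from start to end could differ between periods whatever the diet.

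**Working it through.** **Inputs.** From Sample Size Calculation: reference mean 8.1 mg/kg/min, difference 20%, SD 1.0, alpha 5%, power 80%, N = 20. From Randomization and Blinding: blocks of four by gender. Assumed here, because the protocol does not say: a two-sided test, the SD of the within-person difference, and the size of the period effect.

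**1. The plan's own figure.** The difference is 0.20 x 8.1 = 1.62 mg/kg/min. With the exact paired t test:

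| SD of difference | N for 80% power | Power at N = 20 |
|---|---|---|
| 1.0 | 6 | about 100% |
| 2.0 | 15 | 93% |
| 2.45 | 20 | 80% |
| 2.83 | 26 | 68% |

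N = 20 does not follow from 1.62 and SD 1.0; it follows if the SD of the difference is about 2.45. That is a separate matter, but it means the power loss has to be shown for more than one SD.

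**2. Model.** Let tau be the diet effect on the within-period change, pi the difference between periods in that change, and s the SD of the within-person difference. The expected diet difference is tau + pi in one order (n1 people) and tau - pi in the other (n2 people). A constant shift in level between periods cancels in the change score and is not part of pi.

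**3. Standard error, balanced orders.** The sample variance of the differences becomes about s^2 + pi^2 x N/(N - 1). With k = pi/s, the standard error is multiplied by sqrt(1 + k^2 x 20/19):
- k = 0.5: sqrt(1 + 0.25 x 1.053) = 1.12
- k = 1: sqrt(1 + 1.053) = 1.43

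In simulation at 10:10, type I error of the paired test was 2.9% at k = 0.5 and 0.6% at k = 1. The period-adjusted test stayed at about 5%.

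**4. Bias, unequal orders.** Bias = pi(n1 - n2)/N.
- 11:9 gives 2/20 = 0.1 pi.
- 12:8 gives 4/20 = 0.2 pi. For pi of 10% and 20% of 8.1 (0.81 and 1.62), this is 0.16 and 0.32 mg/kg/min.

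Blocks of four allow an excess of at most two per gender stratum, so 12:8 is the widest split among 20 randomized. Analysis is of completers, so dropout could widen it. The period-adjusted estimate has no bias from pi at any split.

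**5. Power at 10:10 for the stated 1.62 mg/kg/min** (simulated, two-sided 5%):

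| pi, % of 8.1 | SD 1.0 | SD 2.0 | SD 2.45 |
|---|---|---|---|
| 0 | >99% | 93% | 80% |
| 5 | >99% | 92% | 79% |
| 10 | >99% | 90% | 77% |
| 15 | >99% | 87% | 72% |
| 20 | >99% | 81% | 67% |

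The period-adjusted test stays at about 80% in every row of the last column.

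**6. Cost of adjusting when pi = 0.** At 10:10, simulated power is 79.8% adjusted against 80.1% unadjusted. At 12:8 it is about 78% against 80%.

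**The case against.** **Period is not ignored.** An expanded model suggests a base model containing diet and period, and order is in the regressions. The unspecified ANOVA could be a repeated-measures form with order and its interaction with diet, which would adjust for period. The full specification may sit in an analysis plan that is not shown. This stands in part: the means of adjusting are close at hand. But the article names the test for the primary comparison, gives the expanded model as a carryover test, and ties order to regressions introduced for a secondary outcome. Order entered only as a main effect is constant within a participant and cancels from the within-participant diet contrast.

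**Change scores already deal with period.** They remove a level shift, and that limits the concern. They do not remove a period difference in the change.

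**Stronger readings that the documents do not support.**
- A reader might infer that false positives rise. With balanced orders the test is conservative, and at 12:8 simulated type I error was about 5% or lower. It exceeded 5% only with more marked imbalance: at pi = 1 SD, 7.6% at 13:7 and 16% at 14:6. Such splits need dropout or exclusions, for which the protocol gives no rate.
- A reader might infer a collapse in power. A fall to about 17% appears if the diet effect is taken as 0.66 mg/kg/min with SD 1.0 and pi as 20% of 8.1. But 0.66 is only the effect that gives 80% power at N = 20 with that SD; the protocol states 20% of 8.1, which is 1.62.
- A reader might infer that the plan expects a period effect. It says only that one is plausible and might arise.

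**Conclusion.** The point holds as a modest but real weakness in the primary analysis. No statement in the protocol makes the primary estimate period-adjusted, although the protocol itself calls period effects plausible. The larger standard error, and the bias under unequal orders, follow by algebra for any non-zero pi. How much they matter depends on two quantities that the protocol does not give: pi and the SD of the within-person difference. For the stated effect, the loss ranges from negligible (SD 1.0) to about 13 power points (SD 2.45, pi at 20% of 8.1). Larger losses need a true diet effect smaller than the one planned for. Bias is at most 0.2 pi before dropout.

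**What to change.** Name as the primary analysis a cross-over model of the within-period change in clamp insulin sensitivity, with diet and period as fixed effects and participant as random effect. Use the same model for the secondary outcomes. For completers it is equivalent to a two-sample t test, between the two orders, on within-participant period differences, with the contrast halved. If participants with only one period are kept, the two are no longer equivalent: the mixed model uses them and the two-sample test drops them. The plan should therefore say which analysis applies.

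The cost is one degree of freedom, under one power point at 10:10 when there is no period effect (about two at 12:8), and a sentence of analysis text. Visits and measurements do not change.

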### Screening

The study timelines are presented in Figure 1. Female participants will be required to commence metabolic testing while they are in the follicular phase of their menstrual cycle and a urine pregnancy test will be performed to exclude pregnancy. At visit 1, screening will be undertaken by a registered medical practitioner who will collect the medical history and perform a physical examination including measurement of blood pressure, height, body weight, and waist and hip circumference using the methods outlined in the following sections.

At the second visit, participants will undergo an OGTT with measurement of fasting and 2-hour glucose levels to exclude diabetes according to the World Health Organization (WHO) 1999 criteria [20]. Blood samples will be analyzed by a single accredited laboratory for full blood count, kidney and liver function, lipid profile, and C-reactive protein (CRP) as a marker of inflammation. Participants will also be given a 3-day food diary to record their habitual dietary intake and this will be returned on their next visit where it will be used to aid the dietitian in the development of individualized test diets (as following).

### Baseline Assessment

Baseline assessments will commence at the third visit which will involve measurement of blood pressure and body composition by bioimpedance. At the fourth and fifth baseline visits, an intravenous glucose tolerance test (IVGTT) and a hyperinsulinemic euglycemic clamp will be performed (detailed below in Data Collection and Analyses). Participants will complete the International Physical Activity Questionnaire (IPAQ) questionnaire to assess habitual physical activity [21].

### Randomization and Blinding

Following successful screening and baseline assessment, subjects will be randomized by a computer program to commence the study with either the high or low AGE diet. Randomization will be done in blocks of four by gender using a relevant computer program to ensure balance in each test group and will be conducted by a researcher from within our department who is not involved in the trial data collection, analysis, or reporting. Diet type will be coded as (red or blue) by the dietitian, so that participants and blinded investigators remain unaware of which dietary period they are undertaking or how diet might affect glucose metabolism. Clinical and laboratory investigators will also be masked to diet allocation.

